#### Data collection

At baseline data will be collected using paper and pencil. For the follow-up data collection a smartphone application (the study *App*) will be developed to run on iPhone and Android operating systems.

This study App will feature electronic diaries for the days of menstruation (8 days maximum) in which study participants will log daily data on their medication intake, type of complaints, and on compliance (duration and frequency of acupressure) if required. Furthermore, it consists of a questionnaire that will appear after the end of menstruation. All data measurements and time points are listed in Table 2.

**Table 2 T2:** Data collection

	**Baseline**	**Cycle 1**	**Cycle 2**	**Cycle 3**	**Cycle 6**
Sociodemographics (age, migration background, education)	x				
Mean pain intensity on the days with pain (NRS)	x	x	x	x	x
Worst pain intensity (NRS)	x	x	x	x	x
Duration of pain (days)	x	x	x	x	x
Sick leave days	x	x	x	x	x
Intake of medication against menstrual pain	x	x	x	x	x
Adverse events and adverse effects^a^		x	x	x	x
Application of other therapies	x	x	x	x	x
Body efficacy expectation	x	x	x	x	x
Credibility of the intervention^a^				x	
Expectation	x				
Type of menstrual complaints^b^	x	x	x	x	x
Compliance^a,b^		x	x	x	x

^a^Only in the intervention group.

^b^Assessed by the diary.

#### Sample size

A sample size of 86 women per group will have a power of 90% to detect a mean difference of 1.5 points on the NRS (primary outcome) using a two-sided *t*-test with significance level of 0.05. Based on effect size in previous acupuncture studies, we assume a mean of 5.5 in the control group and 4.0 in the intervention group, with a common standard deviation of 3 points. We will include 110 women per group (220 in total) to compensate drop-outs. Sample size calculation was completed with nQuery Advisor 6.02.

#### Data analysis

The primary analysis of the primary outcome will be calculated using an analysis of covariance (ANCOVA), adjusted for baseline NRS value (fixed covariate) to test the null hypothesis of equal means in ‘mean pain intensity at the days of pain during the third menstruation’ between the two treatment groups. The analysis will use the full analysis set (FAS, all available data without imputation of missing values) with a two-sided significance level of 0.05. Results will be reported as adjusted group means with 95% confidence intervals and the *P* value for the group comparison. All further analyses on the primary and all secondary endpoints will be considered explorative and no error adjustment for multiple testing will be done. The secondary outcomes will be analyzed for the FAS similarly to the primary analysis, that is ANCOVA, logistic regression, or Poisson regression (depending on the scale and distribution of the data), adjusted for the respective baseline value (when available). The primary analysis of the primary outcome will be repeated based on the per-protocol population. In addition, missing data on the primary outcome will be imputed by multiple imputation techniques. In case of relevant differences in baseline variables between the treatment groups, the analysis of the primary outcome will be repeated with the additional adjustment for these variables. As supportive analysis, mixed model for repeated measures (MMRM) will be fit to compare the two treatment groups with respect to changes in the primary outcome over time. The model will include terms for treatment and time as fixed main effects, an interaction term for treatment by time, and the subject as a random effect. Further details will be described in the statistical analysis plan. The following subgroups will be considered: migration background (yes/no), age groups, anticontraceptive use (yes/no). A detailed statistical analysis plan (SAP) will be developed prior to any data analyses. Data analysis will be performed in SAS Version 9.2 or higher (SAS Inc., Cary, NC, USA).

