#### Participants

Potential participants will be informed with brochures and posters at universities, colleges, gyms, and doctors’ offices. The study will include women aged 18 to 25 years with dysmenorrhea (defined as cramping pain during every menstrual cycle). Pain has to be moderate or severe and defined as a score ≥6 on the Numeric Rating Scale (NRS) for the worst pain intensity during the last menstruation. Furthermore, to be included in the study women need to have had their menstruation in the last 6 weeks, a duration of menstruation cycles between 3 and 6 weeks, and no prior history of gynecological disease that could be a reason for dysmenorrhea. Additionally, having a smartphone (iPhone or Android) is required.

Women will be excluded if they are receiving or conducting acupressure, acupuncture, Shiatsu-or/and Tuina massage at the moment or are planning to do so in the next 8 months and if they are pregnant or are planning to become pregnant in the next 8 months.

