#### Randomization

If a woman meets all inclusion and no exclusion criteria she will be randomized to either the control (usual care only) or the intervention (usual care plus acupressure) groups by simple randomization with an allocation ratio of 1:1, that is 110:110 participants. The randomization list will be included in a safe Microsoft Access database to ensure that it is not accessible during the randomization process of individual participants. The randomization list will be created in SAS (Version 9.2, SAS Inc., Cary, NC, USA) by a statistician. Randomization process will be conducted by the study office at the Institute for Social Medicine, Epidemiology, and Health Economics. To ensure allocation concealment upon inclusion into the study the stuff enters participants into the database and receives the allocation to intervention or control group.

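### The supportive MMRM lists no baseline pain term and only a random subject effect, so with complete data its cycle-3 contrast is less precise than the primary ANCOVA and not directly comparable with it

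*Protocol article*

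**What the plan says.** All of the analysis text is in the Data analysis section of the protocol article.

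- The primary analysis is an ANCOVA of cycle-3 mean pain, "adjusted for baseline NRS value (fixed covariate"), on available data without imputation.
- Secondary outcomes are likewise adjusted for their own baseline value where there is one.
- The supportive MMRM compares the arms on how the primary outcome develops over time. Its terms are "terms for treatment and time as fixed main effects, an interaction term for treatment by time, and the subject as a random effect". No baseline covariate and no residual covariance structure are named. The text does not say whether baseline is one of the response times. The next sentence leaves further details to the SAP.
- Missing primary-outcome data are also to be handled by multiple imputation. Everything beyond the primary test is explorative.

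Outcomes measurement and Table 2 place mean pain at baseline and cycles 1, 2, 3 and 6. Under Participants, entry requires a score of at least 6 "for the worst pain intensity during the last menstruation".

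**The concern.** The section states its baseline adjustment for the primary and the secondary analyses, then lists the MMRM terms without it. Followed as written, the MMRM is a random-intercept model. Two things follow.

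First, the cycle-3 contrast gives up the precision that baseline adjustment brings, and chance baseline imbalance enters it differently from the primary analysis. If the MMRM and the ANCOVA disagree, a reader cannot tell whether the cause is the use of partial follow-up or the change in adjustment.

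Second, a random subject effect alone fixes one variance for all visits and one correlation for every pair of visits. Cycles 3 and 6 are then as closely correlated as cycles 1 and 2. If baseline is a response, it must also share the follow-up variance, although the entry rule on worst pain may narrow the spread of baseline mean pain.

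**Working it through.** **Inputs from the Sample size section.** The target is stated as "A sample size of 86 women per group will have a power of 90% to detect a mean difference of 1.5 points on the NRS". The planning means are 5.5 (usual care) and 4.0 (acupressure), and the SD is 3 in both arms. Enrolment is raised to 110 per arm to allow for loss. Allocation is 1:1. The document gives no correlations, so every ρ below is an assumption and is shown over a range.

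**The plan's own figure.** With a difference of 1.5, SD 3 and two-sided 0.05, the normal approximation gives 85 per group. The noncentral t gives 86, with power 0.903. The stated 86 reproduces. The planned loss is 110 - 86 = 24 per arm (21.8%).

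**Cycle-3 contrast, 86 per arm, complete data.** With treatment by time in the model and complete data, the estimated contrast is a difference of observed means. With SD 3 at every visit and correlation ρ between baseline and cycle 3:

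- ANCOVA: variance = 2·9·(1-ρ²)/86
- Listed model, follow-up cycles only: variance = 2·9/86; ratio to ANCOVA 1/(1-ρ²)
- Listed model, baseline as a response (change from baseline): variance = 2·9·2(1-ρ)/86; ratio to ANCOVA 2/(1+ρ)

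| ρ | ANCOVA SE | Follow-up only SE | Change from baseline SE | Baseline as covariate SE |
|---|---|---|---|---|
| 0.3 | 0.436 | 0.457 | 0.541 | 0.436 |
| 0.5 | 0.396 | 0.457 | 0.457 | 0.396 |
| 0.7 | 0.327 | 0.457 | 0.354 | 0.327 |

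At ρ = 0.5 the ANCOVA variance is 18·0.75/86 = 0.157, and both readings of the listed model give 18/86 = 0.209. The variance ratio is 1.33 and the SE ratio 0.457/0.396 = 1.15. Power for a 1.5-point difference, Φ(1.5/SE - 1.96), is 0.966 for ANCOVA and 0.906 for the listed model.

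The ratio 2/(1+ρ) needs equal SDs at baseline and cycle 3. With baseline SD s₀ and cycle-3 SD s, the per-woman variance of change is s₀² + s² - 2ρs₀s = s²(1-ρ²) + (s₀ - ρs)². It is never below the ANCOVA variance, but the excess vanishes if s₀ = ρs.

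**With dropout.** Suppose 24 of 110 per arm give cycles 1 and 2 but miss cycles 3 and 6, with all correlations 0.5. The SEs are ANCOVA 0.396, listed model 0.441 (follow-up only) or 0.438 (change), and with a baseline covariate 0.389. With baseline correlation 0.4 to 0.5 and follow-up correlation 0.5 to 0.8, they are 0.421 to 0.441 for the listed model (follow-up only), 0.396 to 0.419 for ANCOVA and 0.368 to 0.408 for the baseline-adjusted model. The listed model then carries 14% to 23% less information than the adjusted one.

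**Where the ordering changes.** At baseline correlation 0.2 with this dropout, the ANCOVA SE is √(18·0.96/86) = 0.448. The follow-up-only model has 0.441 at follow-up correlation 0.5 and 0.421 at 0.8, so it is slightly more precise. For an effect averaged over the four cycles, complete data, the variance without baseline is 18·(1+3ρ)/(4·86). Its SE is 0.362 at ρ = 0.5, below the 0.396 of the cycle-3 ANCOVA. At ρ = 0.6 the order reverses (0.383 against 0.366).

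**Covariance assumption.** The random-intercept model was simulated under serially decaying correlation at times 0, 1, 2, 3 and 6 (decay parameter 0.6 to 0.9, 110 per arm, 6,000 replicates, nominal 0.05).

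- Follow-up-only cycle-3 contrast: model SEs about right, type I error 0.044 to 0.057.
- Change from baseline, equal SDs: model SEs 5% to 7% too small, type I error 0.061 to 0.065.
- Change from baseline, baseline SD 1.5 against 3 later: conservative in the case run, type I error 0.026.

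**The case against.** The strongest reply is that the article defers details to an SAP that is not shown, and that listing what a model includes need not exclude other terms. Covariance structure and degrees of freedom are ordinary SAP matter, and their absence alone would be no finding. What remains is that the article does name terms, names a random subject effect as the only source of dependence, and omits an adjustment that the same section spells out for its other analyses. An SAP that follows this text carries the weaker model forward.

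The text on change over time may mean that baseline is a response. Baseline is then not ignored, but with complete data the cycle-3 contrast is still never more precise than ANCOVA.

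Four stronger readings are tempting, and the document does not support them.

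- A reader might infer that the covariance is wrong for these data. There are no data and no correlations in the document. The entry rule concerns worst pain, not the modelled mean pain. The simulated error rates lie on both sides of 0.05.
- A reader might infer that the MMRM is the main safeguard against attrition. The section separately plans multiple imputation of the primary outcome.
- A reader might infer that the listed model is always less precise than ANCOVA. The cycle-averaged effect and the low-correlation dropout case are exceptions.
- A reader might quote one figure for the information lost. Any such figure rests on assumed correlations.

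**Conclusion.** The point holds in limited form. The listed MMRM omits the baseline adjustment used elsewhere in the plan and implies equal variances and correlations across visits. With complete data its cycle-3 variance exceeds that of ANCOVA by a factor of 1/(1-ρ²), or 2/(1+ρ) if baseline is a response with the same SD. At an assumed ρ of 0.5 that is an SE about 15% larger. Adding baseline removes the loss, and gives a small gain when women with partial follow-up contribute.

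The covariance restriction is a reason to choose a freer structure. It does not show invalid inference. Leaving baseline out of a randomised comparison costs efficiency and comparability, not validity.

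Severity is minor. The analysis is supportive and explorative, and the primary ANCOVA and its error rate are unaffected.

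**What to change.** In the SAP, specify the supportive model as follows:

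- response: mean pain at cycles 1, 2, 3 and 6;
- fixed effects: treatment, cycle, treatment by cycle, baseline NRS and baseline NRS by cycle;
- unstructured within-subject covariance in place of the random subject effect;
- reported result: the cycle-3 treatment contrast with its 95% confidence interval, beside the primary ANCOVA and the multiple-imputation result.

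The cost is one sentence in the plan and a few lines of SAS. An unstructured covariance over four visits has 4·5/2 = 10 parameters, which about 220 women can support. No extra data are needed, since Table 2 already collects baseline mean pain. The SAP is to be written before any analysis, so the change can still be made there.

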#### Ethics

The protocol of the main study was approved by the local ethics review boards (Approval number: EA 1/027/12) and the study itself will be conducted according to common standard guidelines (Declaration of Helsinki, Good Epidemiological Practice, WMA General Assembly, Somerset West, Republic of South Africa, 1996). All study participants will provide written informed consent.

## Discussion

To the best of our knowledge this will be the first study that investigates the effectiveness of additional self-care acupressure against menstrual pain in a Western country. Furthermore we used broad stakeholder engagement [19] to plan a study that is useful for clinical decision-making. Menstrual pain is a common problem with a high socioeconomic burden and the advantage of self-care acupressure implemented through an App is that it is easy to apply in a real-life context. Consequently a pragmatic trial was designed to assist healthcare decision-makers with high quality evidence.

This paper presents the impact of stakeholder engagement on the development of the study design and the resulting study design. Our approach represents two main advantages: input of international experts to develop the study intervention and broad stakeholder engagement for study protocol development.

Results of the survey and the focus group discussion were at some points conflicting and contradicting, for example the different amounts of time women are willing to spend for acupressure. Therefore, the Stakeholder Advisory Group was a key element in the decision making process. Its five main decisions had a significant impact on the study design, resulting in the cancellation of a whole previously planned study arm. All phases of the process were fair and transparent to promote a shared understanding among the various stakeholders. As the number of stakeholders’ increase and the perspectives of the group become more diverse, maintaining such transparency could prove more complicated. It is clear that stakeholder engagement requires investment of people, time, and monetary resources. In the study design presented here the process of stakeholder engagement took 8 months and several researchers were involved.

We observed that the desires of the stakeholders and the consensus of experts about the intervention protocol could be opposing. Whereas the interviewees of the focus group could hardly imagine applying preventive acupressure, the experts found it absolutely necessary to achieve a good treatment benefit. We tried to balance the different perspectives of stakeholders with multiple techniques, but the results of stakeholder engagement might have been different if other stakeholders had participated or we had conducted the survey and focus group discussion at different colleges. Another limitation was that we were not able to include a representative from a health insurance company to participate in the stakeholder advisory group. Furthermore, CER is a new concept in Germany and stakeholders are not accustomed to be invited to support research projects and are not aware of the benefit of their participation. Increased public awareness of a ‘help us to help you’ mentality and an importance placed on stakeholders as decision-makers [23] can increase the enthusiasm and likelihood of engagement in the research process.

When applying the PRECIS criteria to our trial we were aware that most design elements were rated to be in the middle of the effectiveness-efficacy continuum. Whereas patient-centered outcomes and a flexible comparator protocol are more on the effectiveness side of the continuum, monitoring of compliance and treatment protocol are more on the efficacy side. Eligibility criteria are moderately pragmatic with inclusion of a limited range of affected women. Using an App with reminders and compliance measures can be seen as the main reason that our trial score was more in the middle of the efficacy-effectiveness continuum. The PRECIS rating was found to be useful in making the elements of the trial design and its difference from a usual care setting more transparent. We rated the trial in a consensus meeting within the members of the Stakeholder Advisory Group. Had the rating process be carried out independently by the individual stakeholders as described in previous studies [24,25] we may have seen different results. However, when non-scientific stakeholders are included in the rating process our approach, which prioritizes group discussion and consensus, might be more efficient in addressing any questions as they arise.

## Conclusion

Our experience with stakeholder engagement as part of CER was beneficial helping us to develop a study design that meets more of the needs of decision-makers. This includes using an App as a modern tool for both the implementation of the intervention and data collection in a young target group. The subsequent pragmatic randomized trial will investigate the effectiveness of additional self-care acupressure for women with menstrual pain compared to usual care alone. The results will strengthen the evidence on self-care acupressure for menstrual pain.

## Abbreviations

ANCOVA: Analysis of covariance; CER: Comparative effectiveness research; NRS: Numeric rating scale; NSAIDs: Non-steroidal anti-inflammatory drugs; PRECIS: Pragmatic explanatory continuum summary; SAP: Statistical analysis plan
